## Abstract

This proposed study will examine whether structured physical activity reduces the recovery time of cognitive functioning during the early phase of substance use disorder treatment. Addiction or substance dependence is associated with neurobiological changes and cognitive impairment that can affect quality of life and the efficacy of therapy for up to a year after clinical detoxification. The biological, psychological, and social effects of physical exercise have the potential to be a therapeutic approach to increase quality of life and relieve symptoms associated with substance abuse, such as psychosis, depression, and anxiety. There is a dearth of research on physical activity and exercise in clinical substance use disorder patients. This protocol describes a clinical study that will examine cognitive recovery after substance abuse using physical exercise as a treatment intervention. We will use a quasi-experimental longitudinal clinical trial, with a pretest and multiple posttests, on naturally randomized sequential groups. Patients will be consecutively be recruited into the study groups, with a control group that is completed, before its followed by an intervention group, each with 30 patients. Patients will be enrolled 2 weeks after the start of detoxification, at which time all subjects will be inpatients at the Stavanger Salvation Army Treatment Center in the Norwegian specialized healthcare system. Cognition will be evaluated with a comprehensive battery of cognitive tests, including several tests of executive function. Physical fitness will be tested with the Rockport 1-Mile Walk Test, the 30-S Chair Stand Test, the 1-Min Burpee Test at baseline (within the first 2 weeks of admittance) and after 4 weeks. The intervention will be a 30-min workout at 70–90% of maximum heart rate (134–170 bpm), recorded and calculated by a Polar heart rate monitor. The intervention treatment will be administered four times a week for 4 weeks and will consist of high-intensity circuit training, high-intensity interval training, functional movement, and primitive reflex training. We anticipate improvement in both the control and intervention groups, with the exercise intervention group having the greatest increase in recovery of cognitive function because of the combination of functional full body movements and primitive movement training in an intense interval training program.

**Clinical Trial Registration ID:** ISRCTN74750479, Retrospectively Registered.

## Introduction

Substance use disorders (SUD) are among the most prevalent, chronic, and severe diseases in the world in terms of mortality and disability (Kessler et al., 2007), and they are associated with considerable social, economic, and individual health consequences (Adrian and Barry, 2003; Schuckit, 2006; Hasin et al., 2007; Kirby and Sugden, 2007; Wittchen et al., 2011). The combination of impaired physical and mental health among SUD populations is associated with life expectancies that are 20–30 years less than the general population (Stenbacka et al., 2010; Nordentoft et al., 2013). Individuals with SUD have a high tendency for comorbidity. Compared with the general population, the SUD group has more frequent contact with the healthcare system (Richards et al., 1999, 2017; Bernstein et al., 2014) because of a variety of illnesses such as cancer, diabetes, cardiovascular diseases, different kinds of physical trauma, and suicide (Kim et al., 2009; Stenbacka et al., 2010; Nordentoft et al., 2013). Depression, anxiety, attention deficit hyperactivity disorder (ADHD), personality disorder, and psychosis are among the most common comorbidities (Conway et al., 2006; Pennay et al., 2011; Pettinati et al., 2013; Adida et al., 2014; Harstad et al., 2014; Hartz et al., 2014). Individuals with SUD also have a high prevalence of cognitive impairment, which can contribute to low quality of life and the tendency to drop out of treatment (Rosselli and Ardila, 1996; Gouzoulis-Mayfrank and Daumann, 2006; Hagen et al., 2016, 2017a,b, 2019; Topiwala et al., 2017; Hall et al., 2018). A recent study (Hagen et al., 2016) also highlighted the importance of adequate recovery time for cognitive functions. Although pharmacological and psychological interventions are well established in the treatment and the research fields, relapse rates are typically high. The limited success rates of SUD treatments provide a good argument for focusing on adjunct treatments for SUD patients with interventions that target both physical and mental health.

Physical activity may be an excellent adjunct treatment to existing treatment regimens by improving the patient’s function and reducing symptoms. Exercise is a subcategory of physical activity that is planned, structured, repetitive, and designed to improve or maintain physical fitness, physical performance, or health (Caspersen et al., 1985). The general effects of physical activity are most significant when participants transition from an inactive lifestyle to a more physically active lifestyle (Pate et al., 1995; Ekelund et al., 2016). Exercise-based interventions are well established in the mental health service and research fields. Increased physical fitness, positive effects on depression and anxiety symptoms, and fewer negative symptoms for patients with schizophrenia are some of the results from mental health research (Rosenbaum et al., 2014; Haglund et al., 2015). Exercise interventions have also been observed to have positive effects on cognitive functions for severe mental illnesses (Firth et al., 2016), perhaps partially through an impact on brain functioning. Such research constitutes a persuasive argument for the exploration of exercise-based interventions in chronic or severe SUD populations.

However, only a few studies have examined the impact of physical activity or exercise in patients with SUD (Zschucke et al., 2012; Giesen et al., 2015). In September 2017, we conducted a literature search in Embase, Medline, SPORTDiscus, PsycINFO, and CINAHL using the search terms “high-intensity interval training” (HIIT), “high-intensity circuit training” (HICT), “cognitive function,” and “SUD.” The results of our search yielded 11 articles (Weinstock et al., 2008, 2014; Smith and Lynch, 2011; Wolff et al., 2011; Zschucke et al., 2012, 2013; Flemmen et al., 2014; Wang et al., 2014; Haglund et al., 2015; Klika and Jordan, 2015; Unhjem et al., 2016) of relevance to this study. This corpus included research that examined physical activity for SUD populations as outpatients or inpatients in recovery after withdrawal (Zschucke et al., 2012). Physical activity or exercise for SUD populations was shown to improve physical fitness, cardiovascular health, and sleep quality, and reduce the withdrawal symptoms of substance use, as well as anxiety and depression symptoms (Roessler, 2010; Zschucke et al., 2012; Wang et al., 2014; Giesen et al., 2015; Hallgren et al., 2017). It has also been observed that engaging in a physical activity program during treatment can contribute to reduced dropout rates, thereby increasing the success rate of therapy (Weinstock et al., 2014). Although this body of work presents promising results, many of the studies have methodological limitations, such as being pilot studies or lacking control groups. Because of the positive impact exercise can have on mental health, we believe it is extremely important to explore exercise interventions in the clinical treatment and recovery for SUD populations. Preexisting data and approaches in the field of mental health and SUD show great promise; for example, HIIT principles have been found to increase health benefits (Milanović et al., 2015; Unhjem et al., 2016; Karlsen et al., 2017). However, we lack data on dose, intensity, and the most beneficial types of exercise.

1.This study protocol is designed to investigate the impacts of HIIT and HICT combined with functional exercises and primitive reflex training on quality of life and cognitive functioning for patients with SUD. Specifically, the protocol will examine whether structured physical activity improves cognitive functioning for SUD patients relative to that of SUD patients in a control group.2.We will examine whether different intensities of physical activity, such as HIIT/HICT versus other types of physical activity (e.g., hiking) are associated with different cognitive recovery trajectories during the subacute phase of SUD treatment.

This research protocol has several possible applications. First, it will enable future studies to reproduce the exercise protocol and increase the knowledge base on SUD and the effects of exercise. One of the more significant problems in the exercise literature is the inadequate description of exercise, such as the dose, intensity, and how exercises are implemented in studies, which limits reproducibility. This protocol and training regime would serve as a base for comparisons with other workout routines, types of exercises, and duration of exercises. Because this exercise regime will be compared with control group activities, it will be validated as having positive or negative effects for SUD patients in a subacute clinical setting.

Second, because there are so few studies on exercise and substance abuse, a protocol will make it easier to reproduce and increase the number of studies with identical exercise regimes by using this protocol as a guide. This would facilitate comparisons between studies and allow for systematic reviews and meta-analyses.

Third, if this protocol leads to an effective intervention which improves the participants’ cognitive functioning and quality of life, the training regime would be inexpensive and easy to implement in a clinical setting, as there is no need for specialized equipment or extensive staff training.

## Materials and Equipment

### Design

The design of this study is a quasi-experimental, longitudinal clinical trial, with pretest and multiple posttests. The control and intervention groups will be run sequentially, with patients naturally randomly assigned to substance abuse treatment (see below). This study will be conducted in a clinical setting as part of the daily treatment interventions conducted at the Salvation Army Treatment Center, Stavanger (FAB), including testing the efficacy of HIIT for the recovery of cognitive functioning in patients with SUD. After completion of the clinical trial, patients will be followed prospectively for 1 year.

### Control Group

This study will have an active control group of SUD inpatients recruited from the same treatment facility as the patients in the intervention group. The control group will receive treatment as usual (TAU) for SUD patients. The treatment focuses on activities of daily living (ADL), including personal hygiene (e.g., washing oneself and brushing teeth); sleep hygiene, which focuses on regular sleep and wake-up times to help normalize sleep patterns; learning or relearning how to prepare and cook food; eating in a social setting at fixed times; house cleaning and work assignments relevant to making the ward run smoothly; structured socializing and group sessions, twice a day; and structured physical activity in the form of 30–120-min daily hikes and a longer weekly hike for a duration of 3–5 h.

### Intervention Group

Participants in the intervention group will receive the same TAU as the control group, and they will also do four additional 30-min exercise protocols each week.

### Randomization

Although we will not be conducting a true randomized control trial, the control and intervention groups will be run consecutively, and random assignment to these groups will occur naturally because the external allocation system of three separate units allocates patients with different needs to the SUD treatment waiting list independently of each other. Natural allocation will be aided further by SUD patients dropping out of the waiting list for entry to treatment.

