1.Baseline testing. The physical and neuropsychological testing will be conducted within 2 weeks of admittance to the Salvation Army Treatment Center.2.The researchers will not conduct randomization, as there is natural allocation as a result of the SUD treatment allocation system, which will be continuous throughout the study.3.The control group is completed first. Structure is changed in the clinic and intervention group is started up after the last control patient has left the clinic.4.The intervention will consist of the physical exercise protocol, which will be conducted for 4 weeks.5.The final tests of physical function will be conducted the week after the exercise protocol is completed. The prospective follow-up will consist of cognitive testing carried out at 3, 6, 9, and 12 months after the baseline test.6.Discontinuation: Patients that don’t follow the protocol or don’t follow the TAU of the Facility will be discontinued. If they don’t complete the follow up test with in the allocated time line or neglect to perform the test they will be discontinued (Figure 1).

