## Anticipated Results

In this study, we expect the participants in both the control and intervention groups to show progress in physical and mental health after a period of substance abuse. We believe that the data generated in this project will mostly be at the interval or ratio level (whether the rating of perceived exertion is ordinal or interval data will not be discussed here). We will use the mean as a measure of central tendency for the group results for the neurocognitive test, while the reflexes we use frequency and proportions, and the standard deviation to express the spread of results within the group. If useful, the standard error of the mean (SEM) will be used to express the accuracy of the mean value. If the results are highly skewed (skewness > 1.5), we will use a log transformation and geometric mean together with a 95% confidence interval to express central and spread tendencies. To compare results over time from pretest to posttests, and between-group differences, we will use repeated measures ANOVA/*t*-tests with Sidak/Holm *post hoc* tests, where we have collected three or more measurements a linear mixed modeling accounting for the missing data will be used. Group comparisons will be made with an ANOVA/*t*-test for independent groups. If the test of normality should fail (Kolmogorov–Smirnov with Lilliefors correction), the corresponding non-parametric tests will be used, i.e., the Wilcoxon–Mann–Whitney rank sum test for independent *t*-tests and repeated measures ANOVA for ranks (Tukey’s *post hoc* test). Statistical significance will be set at a *p*-value of ≤0.05, and effect sizes will be calculated according to Cohen (1988), with the help of an online effect size calculator (the CEM effect size calculator, Center for Evaluation and Monitoring, Durham University, United Kingdom^1^). An effect size of ≥0.5 will be considered clinically relevant (two-sided). If there is a need for building indexes of different types of scores, *Z*-scores will be used. Based on previously published data on fitness development and depression scores, we should be able to attain statistical power of 0.8 with at least 10 subjects in each of the two groups. Nevertheless, we have set target recruitment at *n* = 30 for each group.

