### Limitations of the Study

Because the intervention and control groups will be run consecutively rather than concurrently, there is the potential for non-equivalent time periods to create bias. However, we chose this approach because previous studies had suffered recruitment failures and high dropout rates. The length of the proposed study is not fixed, and because of our funding and support, this study can continue until the quota for participants is met.

This study is designed to accommodate clinical realities. Thus, different SUD groups are not fractionated during treatment, and the project protocol does not divide different groups of SUD after clinical classification. This may create some problems with the results from baseline because of various issues with the abuse of different drugs and possible side effects that might affect the test results differently. We will account for this Statistically.

Finally, the patient population will be recruited straight out of a detoxification clinic, which will most likely influence the test results. However, this may actually be an advantage, because having access to patients so quickly after controlled, medically supervised detoxification may give us a more accurate picture of their mental status when the patients are at their lowest point in their recovery trajectories.

The Norwegian Ministry of Health and Social Affairs and the Salvation Army of Norway have provided financial support for this study.

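### Groups formed by admission period are described as randomly assigned, and the plan leaves open unadjusted between-group tests alongside analyses that use the pretest

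*Protocol article*

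**What the plan says.** **Allocation.** The Abstract describes a design "with a pretest and multiple posttests, on naturally randomized sequential groups". The Randomization section opens with "Although we will not be conducting a true randomized control trial" and, in the same sentence, claims that "random assignment to these groups will occur naturally because the external allocation system of three separate units allocates patients with different needs". It adds that drop-out from the waiting list helps this natural allocation. Stepwise Procedures, item 3, gives the working rule: the control group is completed, then "Structure is changed in the clinic and intervention group is started up after the last control patient has left the clinic".

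**Analysis (Anticipated Results).** Three routes to a group difference are named:
- repeated-measures ANOVA or t-tests from pretest to posttests, with a linear mixed model where there are three or more measurements;
- "Group comparisons will be made with an ANOVA/*t*-test for independent groups";
- if a normality test fails, "the corresponding non-parametric tests will be used", namely the Wilcoxon–Mann–Whitney test or a repeated-measures ANOVA on ranks.

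Nothing says which route gives the main between-group result.

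**Limitations.** The section concedes that non-equivalent time periods may cause bias. On mixed drug use and its effect on test results it says "We will account for this Statistically".

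**The concern.** The two reasons given for random assignment are independent referral by three units and attrition from the waiting list. Both affect who is admitted and when. Neither is a chance mechanism that sends a given patient to control or exercise. The units are said to refer patients with different needs, and attrition from a waiting list is a possible source of selection.

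The wording matters because it supports a causal reading: the Discussion frames cognitive change as directly due to the activity. If readers accept that the groups were randomised, an unadjusted t-test looks adequate. If they were not, any difference between the two periods in baseline cognition, substance mix or clinic practice enters the estimated exercise effect. An unadjusted post-test comparison is then the most exposed of the planned options, unless the baseline difference fades by follow-up.

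**Working it through.** **Step 1. The allocation statements side by side.** Under Stepwise Procedures no calendar time contains both groups. Given the admission date, the probability of being in the intervention group is 0 or 1. That is incompatible with random assignment, however referrals arrive.

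**Step 2. Which outcomes reach which analysis.** Cognition is tested at baseline and at 3, 6, 9 and 12 months: five occasions, so the mixed model applies. Fitness is tested at baseline and in the week after the programme: two occasions, so it gets repeated-measures ANOVA or t-tests. With two occasions the group-by-time test is the t-test on change scores. The independent-groups and rank-sum tests remain available for either outcome.

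**Step 3. Bias under no exercise effect.** The plan gives no figure for imbalance or correlation, so these are assumptions. Let D be the baseline difference in SD units, r the pre-post correlation, P a shift that affects only the second period's follow-up scores, and SD = 1.

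| Scenario | Post-test only | Change score | ANCOVA |
|---|---|---|---|
| D shrinks by r | rD | −(1−r)D | 0 |
| D is stable | D | 0 | (1−r)D |
| Period shift P | P | P | P |

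For D = 0.5, shrinking: post-test bias is 0.25 (r = 0.5) or 0.35 (r = 0.7), and change-score bias is −0.25 or −0.15. For D = 0.5, stable: ANCOVA bias is 0.25 or 0.15.

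**Step 4. False-positive rates.** Simulated trials, 30 per group (the plan's target), two-sided 0.05, D = 0.5; first figure r = 0.5, second r = 0.7:

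| Scenario | Post-test t-test | Change score | ANCOVA |
|---|---|---|---|
| D shrinks by r | 16%, 27% | 16%, 11% | 5%, 5% |
| D is stable | 48%, 48% | 5%, 5% | 18%, 12% |

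At D = 0.3, shrinking, r = 0.7, the rates are about 12%, 7% and 5%.

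**Step 5. A pure period shift.** With P = 0.3 and no baseline difference, all three estimates are biased by about 0.30 SD. The unadjusted t-test then rejects in about 21% of trials. ANCOVA rejects more often (26% at r = 0.5, 35% at r = 0.7), because it estimates the same bias more precisely.

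**Step 6. Power at the plan's relevance threshold, d = 0.5, no imbalance.** The residual variance relative to the post-test analysis is 2(1−r) for change scores and 1−r² for ANCOVA.
- Post-test t-test: 48%.
- Change score: at r = 0.5 the factor is 1.00, so power is again 48%; at r = 0.7 it is 0.60, and power is about 69%.
- ANCOVA: at r = 0.5 the factor is 0.75, an effective 30/0.75 = 40 per group and power of 59%; at r = 0.7 it is 0.51, an effective 30/0.51 = 58.8 per group and power of about 76%.

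**The case against.** The article is open about much of this. It calls itself quasi-experimental, disclaims a true randomised trial, names period bias as a limitation and promises to handle type of drug. A condensed article may leave covariates and model terms to an analysis plan that is not shown, so the lack of a covariate list is not a fault.

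Four stronger readings are tempting and not supported:
- *That every comparison is unadjusted and the baseline is wasted.* Repeated-measures ANOVA and the mixed model both use the pretest, and cognition falls under the mixed model. The 16–27% rates belong only to the post-test branch, and at r = 0.7 most of the power gain over a post-test t-test is already available from change scores.
- *That baseline adjustment restores a 5% error rate.* This holds only if the imbalance shrinks by r; a stable case-mix difference reverses the ranking.
- *That adjustment can cure the period problem.* It cannot, because no period contains both groups.
- *That the rank-based repeated-measures ANOVA is a Friedman test and so ignores the group-by-time question.* The article does not name the procedure.

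Two things stand. Disclaiming a true randomised trial does not repair a claim of random assignment in the same sentence. And the independent-groups and rank-sum tests are named without precedence, although neither uses the baseline and the rank-sum test cannot carry the drug-type adjustment.

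**Conclusion.** The point holds in this form. The statements that patients are randomly assigned, or naturally randomised, are wrong on the document's own account of how the groups are filled, and period and group cannot be separated. On the analysis side the fault is narrower: unadjusted tests are left open beside better ones, and nothing says which governs.

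Under a 0.5 SD imbalance, the post-test t-test rejects a true null in 16–27% of trials if the imbalance shrinks and in about 48% if it is stable. The pretest-based methods range from 5% to 18%, depending on method and scenario. These figures rest on assumed imbalance and correlation, normal data and complete follow-up. They show sensitivity and do not predict this trial's error rate. Since neither ANCOVA nor change scores is generally unbiased without randomisation, agreement between them is worth reporting, but a period effect on follow-up scores would bias both alike.

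**What to change.** 1. **Wording.** Remove the randomisation claims from the Abstract and the Randomization section. Call the study a non-randomised sequential-cohort comparison and report baseline differences between the cohorts. State that period confounding cannot be removed, so a group difference cannot be attributed to exercise alone.

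2. **Main analysis.** For every outcome, name one baseline-adjusted model in place of the unadjusted t-test and rank-sum branches.
   - Cognition: a mixed model with group, visit and group-by-visit.
   - Two-visit fitness outcomes: ANCOVA, or a mixed model with baseline kept as a response. ANCOVA, or any model of post-baseline scores only, uses completers; with baseline as a response, patients without a post-test still contribute.
   - If baseline is a response, say whether the groups share one baseline mean (an ANCOVA-type contrast) or have separate means (a change-type contrast).
   - Include age and, where recorded, substance-type measures such as AUDIT and DUDIT. The article does not say that primary substance is recorded, so this needs checking.
   - If residuals are non-normal, use bootstrap or permutation inference on the same contrast.

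3. **Sensitivity.** Report a change-score analysis beside the main model. If the main model is itself of change type, report ANCOVA instead.

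Cost: edits to the text, a few degrees of freedom and slightly more analysis work. Baseline scores are already collected. Unmeasured period confounding remains and has to be stated with the result.
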